### 2.9. Intervention Assignment

Sequence generation: One-to-one allocation to study groups based on computer generated randomisation sequences with random block sizes. Groups will be stratified into ≤26, >26 and <28 weeks and ≥28 to <31 weeks gestation.

### 2.10. Concealment Mechanism

Randomisation will occur via sequentially numbered brown opaque sealed envelopes containing laminated colour cards to reveal the intervention. The colour code cannot be determined without opening the envelope. Multiples will be randomised as individual participants.

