### 2.8. Sample Size

Data from an observational study indicated that 60% of infants that received DCC and did not breathe received a blood transfusion. This compared to 30% transfused in the group that breathed during DCC. Aiming for a similar 50% relative reduction in the proportion transfused would require 100 infants whose primary outcome could be assessed. To allow for cases where outcome assessment may not be possible (deaths, surgical transfer), 120 infants are to be randomised (60 per group). (A total of 100 would give the study 85% power at a two-sided significance level of 0.05). For a secondary composite outcome of death, CLD or severe IVH, the sample size would allow a 36% difference in outcome to be detected (80% power, significance 0.05), assuming the percentage of infants with a composite endpoint will be 58% (based on historic data).

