### 2.14. Statistics

Initial chi-square tests for categorical data. Numeric data are to be analysed with Mann–Whitney non-parametric statistics or t test if normally distributed. Secondary analysis is planned using logistic regression (IBM SPSS Statistics 26, IBM Corporation 2020, New York, NY, USA). Two-sided probability (*p* value) < 0.05 will be used to indicate statistical significance.

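### The named tests ignore both the individual randomisation of siblings and the gestation strata; the primary p value stays near nominal or mildly conservative, at some cost in precision

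*Protocol article*

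**What the plan says.** Three sections of the protocol article bear on this.

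- Section 2.10 (Concealment Mechanism): "Multiples will be randomised as individual participants". Siblings may therefore fall in the same arm or in different arms.
- Section 2.9 (Intervention Assignment): "One-to-one allocation to study groups based on computer generated randomisation sequences with random block sizes", and "Groups will be stratified into ≤26, >26 and <28 weeks and ≥28 to <31 weeks gestation". Block sizes are not given. Siblings share a gestation and hence a stratum.
- Section 2.14 (Statistics): "Initial chi-square tests for categorical data" and "Numeric data are to be analysed with Mann–Whitney non-parametric statistics or t test if normally distributed". It adds "Secondary analysis is planned using logistic regression", without naming covariates or a term for siblings.

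The primary comparison is a proportion (Section 2.6), so the chi-square test is the one that applies to it. Section 2.8 counts infants and does not mention siblings. The article does not state an expected share of multiples or a within-pair correlation.

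**The concern.** The design puts two kinds of structure into the data, and the named tests use neither.

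**Siblings.** Infants of one pregnancy share gestation, maternal factors and much of their clinical course, so their transfusion outcomes are likely to be correlated. Chi-square, Mann–Whitney and t tests assume independent observations.

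**Strata.** Allocation is balanced within gestation bands, and transfusion risk probably falls with gestation. A comparison that ignores the bands counts between-band variation as noise, although the design has removed most of it from the treatment contrast.

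At stake are the calibration of the primary p value and interval, and precision in a trial sized at 100 assessable infants. The direction of the error also matters: a test that is too liberal would be more serious than one that is slightly too cautious.

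**Working it through.** **1. The plan's own figure.** Section 2.8 gives "60% of infants that received DCC and did not breathe received a blood transfusion" and "This compared to 30% transfused in the group that breathed during DCC", with 100 assessable infants, two-sided 0.05 and 85% power. With 50 per arm and pooled variance under the null, power = Φ[(0.30 − 1.96·√(2·0.45·0.55/50)) / √((0.6·0.4 + 0.3·0.7)/50)] = 86.6%. The stated power is reproduced to within 2 points.

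**2. Effect of sibling pairs on the standard error.** Let f be the share of infants in pairs with both members randomised, ρ the within-pair correlation, and c the probability that a pair shares an arm. For the unadjusted difference,

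true variance / independence variance = 1 + f·ρ·(2c − 1).

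f and ρ are assumptions. For c, simple individual randomisation gives 1/2. Two envelopes from one block of size b share an arm with probability (b/2 − 1)/(b − 1), which is 1/3 for b = 4 and 2/5 for b = 6. Neighbouring envelopes that straddle two blocks give 1/2. A range of 1/3 to 1/2 is therefore reasonable unless blocks of two are common.

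| f, ρ | c = 1/2 | c = 1/3 | c = 1 (all pairs in one arm) |
|---|---|---|---|
| 0.2, 0.5 | √1.000 = 1.00 | √0.967 = 0.983 | √1.10 = 1.049 |
| 0.3, 0.7 | √1.000 = 1.00 | √0.930 = 0.964 | √1.21 = 1.100 |

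Entries are true SE / ordinary SE. Over c from 1/3 to 1/2 the ordinary SE is too large by 0 to 1/0.964 − 1 = 3.7%. At c = 1/3 the implied two-sided error, 2·[1 − Φ(1.96/ratio)], is 0.046 and 0.042. The last column needs every pair to share an arm. With 10–15 pairs and coin-flip allocation, that has probability 0.5^10 ≈ 0.001 to 0.5^15 ≈ 0.00003, and less with blocks.

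**3. Simulation of the plain chi-square test.** N = 100, 12,000 null replicates, Monte Carlo error about 0.002, no difference in risk between strata.

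| Setting | Type I error | True SE / model SE |
|---|---|---|
| No twins | 0.053–0.056 | 1.00–1.01 |
| 30% in pairs, ρ = 0.6, simple allocation | 0.055 | 1.02 |
| 30% in pairs, ρ = 0.6, stratified blocks | 0.049–0.052 | 0.99 |
| 60% in pairs, ρ = 0.9, stratified blocks | 0.042–0.043 | 0.95 |
| 30% in pairs, ρ = 0.6, pairs kept in one arm (not this design) | 0.072 | 1.09 |

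Power at 60% v 30% stayed at about 86–88% in all individual-allocation settings.

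**4. Effect of ignoring the strata.** If strata are balanced by design, true variance / ordinary variance ≈ 1 − V/[p̄(1 − p̄)], where V is the between-stratum variance of risk. Stratum risks are not in the article. As an illustration, assume risks of 0.70, 0.50 and 0.30 with weights 25%, 25% and 50%:

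- p̄ = 0.175 + 0.125 + 0.15 = 0.45
- V = 0.25·0.25² + 0.25·0.05² + 0.5·0.15² = 0.0275
- V/(0.45·0.55) = 0.0275/0.2475 = 0.111
- SE ratio = √0.889 = 0.943, and type I error = 2·[1 − Φ(1.96/0.943)] = 0.038

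A separate simulation under assumed stratum risks gave chi-square type I error of about 0.02–0.04, and power 1–2 points below a stratum-adjusted analysis. Effects 2 and 4 overlap, because shared gestation is part of why siblings correlate, so they should not simply be added.

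**The case against.** The strongest reply has three parts.

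*The error is small and in the safe direction.* This stands. A reader might infer from the independence assumption that p values are too small, or that the trial needs more infants. The article does not support that: the familiar inflation belongs to designs that keep siblings in one arm, and Section 2.10 does the opposite. A reader might also infer that the direction is wholly unpredictable. For the one allocation actually realised there is some truth in this. With 10–15 pairs, chance variation in the number of split pairs moves the SE ratio over about 0.96–1.03 (f = 0.2, ρ = 0.5) or 0.92–1.05 (f = 0.3, ρ = 0.7). On average, however, it is neutral to conservative.

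*The assumed share of pairs is probably high.* This also stands. Section 2 expects about half of infants not to be breathing regularly at 15 s, and Section 2.2 excludes others. If a co-twin qualified independently with probability 0.5, f = 20–30% would require 40–60% of randomised infants to be multiples. Correlated eligibility would lower that figure.

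*Sibling handling may be left to an analysis plan that is not shown.* This stands only in part. The full plan may specify the later logistic model, but Section 2.14 names the tests, and in ordinary form they use neither the strata nor the siblings.

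One argument for a stronger remedy also needs limiting. With known correlation on a linear scale, weighting for siblings would cut variance by about 7% (f = 0.2, ρ = 0.5) to 22–24% (f = 0.3, ρ = 0.7). Those are best cases. An exchangeable GEE proved unstable with only 10–15 pairs, so that gain cannot be counted on.

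**Conclusion.** The point holds in a limited form. The tests named in Section 2.14 do not reflect the individual randomisation of siblings or the stratified allocation. False positives are not materially inflated, and 100 assessable and 120 randomised infants remain adequate on the plan's own assumptions. The cost is an ordinary standard error too large by about 0–4% on average from siblings, a further conservative shift from ignoring the strata, and a point or two of power.

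This rests on assumed values: 20–30% of infants in pairs with both randomised, correlation 0.5–0.7, same-arm probability between 1/3 and 1/2, and transfusion risk that differs by gestation band. Triplets were not simulated; the same offsetting argument applies. Sibling correlation also affects within-arm intervals and the standard errors of shared covariates, such as gestation, in the logistic model.

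**What to change.** In Section 2.14:

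- Make the primary comparison of the proportion transfused a model adjusted for the gestation stratum, for example modified Poisson, or logistic with a standardised risk difference.
- Use small-sample cluster-robust standard errors by mother, under an independence working correlation.
- Use the analogous stratum-adjusted, mother-clustered analysis for numeric outcomes.
- Keep the chi-square test as a supporting analysis.
- Report how many sibling sets had all randomised members in one arm and how many were split.

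Fixing this before the data are seen also removes a later choice between clustered and unclustered results. The precision gain comes mainly from the stratum adjustment. The clustering corrects the standard error but, under an independence working correlation, does not exploit within-pair comparisons.

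The cost is slightly more analysis work and a mother identifier in the dataset. Design and sample size are unchanged. If few sibling sets have two or more infants randomised, the clustering will change little.

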### 2.11. Implementation

The envelope will only be opened once the resuscitation team leader instructs the research assistant to do so. The infants study number will be documented on the birth record and delivery data collection sheet.

### 2.12. Masking

The laminated coloured card and completed randomisation data sheet will be placed in a secure box located in a locked office (only accessible to the research nurse collecting and entering the blinded data into a secure data base). Outcome assessment will be carried out by members of the study team without knowledge of the intervention group.

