
**P** preterm infants < 31 weeks undergoing DCC who did not establish regular respiration by 15 s were randomised to the 

**I** intervention of the T piece intermittent positive pressure ventilation (IPPV) with 30% oxygen compared to the 

**C** control group who received standard care during DCC without IPPV.

**O** outcome assessment was blood transfusion.

**T** time during the neonatal admission.

We anticipated several problems with the study implementation:

*Ergonomics*: Birth, and particularly very preterm birth, is a stressful time with space and equipment limitations. Other investigators have used purpose-built resuscitation trolleys, radiant warmers or other surfaces for infant assessment and management [12,22,23]. However, as described in the “Methods”, we used heated towels on the mother’s thighs or placed the infant at the foot of the bed for vaginal births. We had one skilled operator in charge of the infant who stood next to the surgeon, and in our preliminary trials, this pragmatic approach was satisfactory.

*Monitoring*: Ideally, heart rate and pulse oximetry and temperature should be continuously monitored during this short transition. A recent study found dry electrodes to be the quickest tool for monitoring heart rate (median 13 s) followed by ECG (42 s) and pulse oximetry (105 s). The dry gel electrodes for preterm infants are not yet commercially available and the other methods are too slow for this short period [9,24]. Similarly, with only one neonatal attendee, we could not routinely auscultate or palpate the heart rate. This meant we had to rely on the observation of breathing, activity, tone and colour for monitoring.

*Sterility*: Apart from the neonatal attendee who wore sterile theatre attire, the only contact with the sterile field was the sterile plastic wrap, respiratory circuit and T-piece. A local supplier was able to gas sterilise these components for caesarean deliveries.

*Randomisation and time*: The decision to randomise was undertaken at 15 s and intervention was started by 20 s (this is described in detail below). In simulation testing, we could achieve this with opaque sealed numbered envelopes if we used a colour coded card in the envelope. One of the reasons we did not want to prolong the total DCC time beyond 50 s was because of the safety of the mother and difficulties of safely monitoring potentially compromised infants.

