### 2.3. Interventions

Infants that receive DCC are eligible for randomisation at 15 s of age if breathing (chest wall movement) appears irregular or absent, but the infant is not otherwise compromised (see below). A control group receiving standard treatment will be compared to an intervention arm. Standard treatment consists of the infant being placed supine with the head in a neutral breathing position, placed in a thermal wrap whilst receiving gentle stimulation (face dried, touching or rubbing the torso or back) and completing 50 s DCC. Infants randomised to the intervention arm will receive breathing support in the form of intermittent positive pressure ventilation (IPPV) and continuous positive airway pressure (CPAP) delivered by appropriate mask and T-Piece in addition to standard treatment as described above (Figure 1).

The designated resuscitation team leader (RTL) will collect a sealed, numbered, stratified randomisation envelope for eligible infants < 31 weeks and discuss the study with the midwife and obstetric team antenatally or before delivery.

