### 2.5. Procedure

Time keeping: Timers will be started when “baby out” is announced. The research assistant will call out “15 s” and the RTL will respond by announcing “open/randomise” or indicate not to open the randomisation card once the breathing has been assessed. The research assistant will announce when 50 s has elapsed to clamp the cord.

Randomisation will take place after applying thermal wrap, placing infant supine in a neutral position (see above) and assessing breathing as follows: Apnoeic infants or those that do not have sustained respiratory effort but no pallor and appear well perfused with reasonable tone are eligible.Infants born compromised (apneic, pale, flaccid) and deemed in need of immediate resuscitation are not eligible and have the cord clamped and standard resuscitation commenced [27].

Infants who appear vigorous, with sustained breathing (chest wall movement) at 15 s of age are not eligible for randomisation and neither are infants who initially establish respiration and then became apnoeic after 15 s.

Standard treatment is indicated by a white laminated card whilst the intervention arm is indicated by a blue laminated card (intervention as previously described). During the 50 s DCC, the procedure may be terminated for safety concerns (abruption, clinical deterioration of the mother or infant). After the cord is cut, the infant is placed into a sterile cot (caesarean section) and transferred to a heat table; after vaginal births, the infant will be placed directly onto the heat table. The attending RTL performs the procedure for multiples and a second attendant continues cares after the completion of cord clamping. Oxytocin is to be given after the completion of 50 s DCC for all deliveries as per standard obstetric practice. Standard delivery room management includes humidified Hudson bubble CPAP (6–8 cm; Fisher & Paykel, Auckland, New Zealand) skin servo temperature control, heart rate and saturation monitoring.

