### 2.7. Secondary Outcomes

Apgar scores and delivery room resuscitation including the requirement for endotracheal intubation.Core axillary temperature (digital electronic thermometer) at 5 min of age and on admission to NICU.Respiratory support including surfactant, length and type of support.Transitional circulation assessed based on blood pressure recorded from arterial lines where possible or peripheral recordings if no arterial lines, acid base, lactate, echocardiogram performed within first 6–12 h if possible, inotropes received (first 48 h) and patent ductus arteriosus treatment rates during neonatal admission.Phototherapy received (requirement based on local guidelines) haemoglobin levels on days 1 at 24 h of age and days 2, 3 and 7 (from capillary or venous FBC as preference or capillary gas).Neonatal outcomes as defined by local neonatal network coding criteria [28]. These include: chronic lung disease (CLD) defined as respiratory support or oxygen received at 36 weeks corrected gestational age, discharge home with oxygen, intraventricular haemorrhage (IVH) rates (grades III and IV and any grade reported) within first 24 h if possible, day 5 and day 28 cranial ultrasound, necrotising enterocolitis (NEC) defined by modified Bells stage 2 or higher, retinopathy of prematurity (ROP) highest stage recorded and requiring laser therapy, early onset sepsis (EOS) < 48 h of age and late onset sepsis (LOS) defined by positive blood culture or cerebrospinal fluid after 48 h, death during neonatal admission and length of hospital stay in days [28].Neurodevelopmental outcome at 2 years of age (for infants ≤ 29 week gestation).

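### Section 2.12 claims masked outcome assessment without exception, but the delivery room outcomes listed first in section 2.7 arise where the allocation is openly shown

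*Protocol article*

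**What the plan says.** Section 2.12 (Masking) of the protocol article makes one general statement about outcomes: "Outcome assessment will be carried out by members of the study team without knowledge of the intervention group". The only mechanism it describes is that the card and the completed randomisation sheet go into a secure box in a locked office.

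Section 2.7 opens the secondary outcomes with "Apgar scores and delivery room resuscitation including the requirement for endotracheal intubation". The abstract also names requirement for resuscitation first among the secondary outcomes.

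The procedure at birth is open:

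- Section 2.11: "The envelope will only be opened once the resuscitation team leader instructs the research assistant to do so".
- Section 2.5: "Standard treatment is indicated by a white laminated card whilst the intervention arm is indicated by a blue laminated card".
- Section 2.3: breathing support in the intervention arm is "delivered by appropriate mask and T-Piece in addition to standard treatment as described above". The control arm has no mask or T-piece, and no sham is described.
- Section 1, on ergonomics: "We had one skilled operator in charge of the infant who stood next to the surgeon".
- Section 2.5, on care after clamping of multiples: "The attending RTL performs the procedure for multiples and a second attendant continues cares after the completion of cord clamping". This attendant is not described as masked.

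The only other statement about masking is in section 1, under outcome and sample size. There the day-to-day attending staff are called blinded, in support of the later decision to transfuse.

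**The concern.** A masking statement with no exceptions covers every outcome in section 2.7. The first of these is a set of clinical judgements and decisions made within minutes of birth, by or alongside people who have just seen the card and given or withheld ventilation. Locking the card away afterwards cannot mask a score or decision that already exists.

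What is at stake is how a delivery room difference may be read. Section 2.14 applies a two-sided threshold of p < 0.05. If intubation or Apgar scores differ at that level, the result could be presented as an early effect of assisted breathing under a safeguard that these outcomes did not have. Knowledge of the arm could account for some or all of such a difference, and the analysis could not separate the two.

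**Working it through.** The plan gives no figure on this point: no expected intubation rate, no Apgar distribution and no bound on assessor bias. There is nothing to reproduce, so the check is to set the sections side by side in time order.

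| Time from birth | Event | Source | Is the arm known in the room? |
|---|---|---|---|
| 15 s | Breathing assessed; team leader calls for the envelope; research assistant opens it | 2.5, 2.11 | Yes, from this point (white or blue card) |
| By 20 s to 50 s | 50 − 20 = 30 s of T-piece ventilation in one arm, positioning and stimulation in the other | Abstract, 1, 2.3 | Yes, visibly |
| 50 s | Cord clamped; infant moved to the heat table | 2.5 | Yes |
| After 50 s | Delivery room resuscitation and any intubation; Apgar scores | 2.7 | No change of team and no masked assessor described |
| After the sheet is completed | Card and sheet locked away | 2.12 | Masking can start only here |

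**Resuscitation and intubation.** These are decisions of the team caring for the infant in the delivery room. The team leader called for the envelope and managed the infant during the delay in clamping. The second attendant mentioned for multiples takes over in the same setting. For this component, knowledge of the arm follows closely from the described procedure.

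**Apgar scores.** The article does not say who scores them or at which minutes. That the scorer knows the arm is inferred from the open card, the visible ventilation and the absence of any described masked scorer. The inference is reasonable but weaker than for intubation.

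**Can section 2.12 be read so that it is true of these outcomes?** If assessment means later extraction from records, the sentence may be literally correct. The masked extractor would then only copy a score or decision already made by the birth team, so the masking gives the value no protection.

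**Does another section supply the exception?** No. The blinding in section 1 concerns day-to-day staff and the transfusion decision. No section exempts the delivery room outcomes.

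**Primary outcome.** Transfusion is decided during the neonatal admission, under a guideline that section 2.6 keeps unchanged, by staff whom section 1 describes as blinded. The sequence above does not touch it.

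**The case against.** Four arguments on the other side deserve weight.

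1. *Masking the delivery is hardly feasible.* This stands. The fault lies in the unqualified sentence, not in the open delivery.

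2. *The article describes the open delivery plainly.* This also stands. A careful reader can see that the birth team knows the arm, so it would be too strong to say that the article assures readers that bias cannot occur. The correction is still needed, because a results paper could carry the sentence in 2.12 forward as written.

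3. *A journal article condenses the full protocol, and naming the Apgar scorer is a detail left to that document.* This is fair for the scorer, and the Apgar part is stated here as inference. It does not answer the main point, which concerns a positive statement that the article's own procedure does not support, rather than an omission.

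4. *The consequence is limited.* Correct. Neither transfusion nor the composite of death, chronic lung disease or severe intraventricular haemorrhage, the only secondary outcome with a power statement, is a delivery room judgement. Being listed first is not a declared ranking, and no section says that delivery room outcomes will be used as proof of efficacy.

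A reader might infer more: that the outcome will be biased, or that the false-positive rate can be put at a given level. The document does not support either. Suppose, purely as assumptions, 60 per arm, no true effect and a control intubation rate of 20 to 40%. A 5-point shift in decisions then gives p < 0.05 in about 9 to 11% of trials, and a 10-point shift in about 21 to 33%, against a nominal 5%. These figures restate the shift that was put in. The document bounds neither the shift nor the rate, so they are no estimate for this trial.

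**Conclusion.** The point holds in a limited form. The masking stated in section 2.12 is not a property of the design for delivery room resuscitation and intubation and, by inference, for Apgar scores. These outcomes are open to bias from knowledge of the arm. Its size cannot be computed from the document, and its presence is a risk rather than a demonstrated fact. The primary outcome is unaffected.

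The conclusion assumes that the delivery room team decides on resuscitation and intubation, which the procedure makes close to certain. For Apgar scores it also assumes that no masked scorer exists beyond what the article describes. A fuller protocol naming such a scorer would remove the Apgar part and leave the rest. The correction is worth making because it settles what the trial may conclude from these outcomes and costs almost nothing.

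**What to change.** - **Section 2.12:** limit the masking statement to outcomes ascertained after the delivery room.
- **Section 2.7:** label Apgar scores, delivery room resuscitation and intubation as unmasked, to be interpreted as such and not cited alone as evidence of benefit.
- **Optional:** section 2.5 already makes "heart rate and saturation monitoring" part of standard delivery room management. Recording the monitor readings at a fixed time would add a supporting measure free of scoring judgement. The text should say that these values still reflect care given by the unmasked team, so they reduce the scoring problem without removing the wider one.

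The cost is about one sentence in each section and, if the option is taken, two values on the existing delivery data collection sheet. Treatment, sample size and the primary analysis do not change. The downside is that the delivery room results carry less weight in the report.
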